## Abstract

**Introduction**: Mental disorders, particularly depression and anxiety, represent a leading source of morbidity and disability in young adults, a group increasingly exposed to cumulative psychological processes and environmental stressors. Although evidence links healthy dietary patterns with improved mental health symptoms, the specific contribution of nut consumption (rich in anti-inflammatory, antioxidant, and neuroprotective compounds) remains insufficiently examined in this population. Current evidence also lacks robust data on the dose–response effects of nut consumption and mechanistic pathways involving biomarkers relevant to brain function and mental health. The Nuts4Brain-RCT will investigate the impact of a 6-month mixed-nut consumption intervention on mental health symptoms, cognitive functioning, sleep quality, overall well-being, health-related quality of life, and biochemical brain function mediators in young adults. **Methods and analysis**: A 6-month, randomized, single-blinded, three-arm, dose–response, parallel-group clinical trial will be conducted with 135 university students aged 18–24 years from the University of Castilla-La Mancha, Cuenca, Spain. The participants will be randomly assigned in a 1:1:1 ratio to one of three groups: (1) a control group maintaining their habitual diet while avoiding nut consumption; (2) a 30 g/day mixed-nut consumption group; or (3) a 60 g/day mixed-nut consumption group. The nut consumption intervention will include unsalted, unroasted walnuts, almonds, hazelnuts, and pistachios. The primary outcomes will include depressive (BDI-II) and anxiety (GAD-7) symptoms, perceived stress (PSS-10), cognitive performance (NIH Toolbox), and plasma brain-derived neurotrophic factor (BDNF). Assessments will take place at baseline and at 3 (intermediate), 6 (end of intervention) and 12 months (follow-up). Repeated-measures mixed-effects models will be applied to estimate the effects of nut consumption and dosage on mental health outcomes. **Ethics and dissemination**: The study adheres to the principles of the Declaration of Helsinki and the Singapore Statement on Research Integrity and obtained approval from the Clinical Research Ethics Committee of the Virgen de la Luz Hospital, Cuenca, Spain (REG: 2025/E0125). The findings will be disseminated through high-impact open-access peer-reviewed publications, presentations at scientific conferences, and social media platforms. **Trial registration**: ClinicalTrials.gov. **Identifier**: NCT07292610.

## 1. Introduction

Mental disorders, especially depression and anxiety, are among the leading causes of morbidity and disability in young people worldwide [1,2]. According to estimates from the Global Burden of Disease Study, in 2023, approximately 322 million individuals were living with depressive disorders and 470 million with anxiety disorders, representing the second and sixth leading contributors, respectively, to the overall disease burden among youths aged 10–24 years [1,2]. Recent trend analyses underscore the growing urgency of addressing mental health conditions among young people, revealing a significant upward trajectory [1,3,4]. This increase has been linked to a combination of cumulative stressors, including academic pressures, social expectations, economic uncertainty, and the pervasive influence of digital technology, which have been further intensified by the coronavirus disease 2019 (COVID-19) pandemic [5]. In Spain, suicide has become the leading cause of death among individuals aged 12–29 years, and recent government surveys indicate that nearly half of university students (49.4%) experience depressive symptoms [6,7]. These findings highlight the critical need for timely, comprehensive, and targeted intervention strategies for this vulnerable population [8].

Despite the urgent need for effective management, depression and anxiety remain difficult to address because of their multifactorial etiology, which is characterized by a dynamic interplay of biological, psychosocial, and environmental factors [9]. Conventional pharmacological treatments, such as antidepressants and anxiolytics, often have limited efficacy and may be accompanied by undesirable side effects [10], highlighting the need for alternative or complementary nonpharmacological therapeutic approaches, such as promoting healthy lifestyles, including a healthy diet [10]. In this context, scientific evidence from observational [11] and clinical trials [12] has shown that healthy dietary patterns, including the Mediterranean diet, are consistently associated with reduced risks of depression and the alleviation of its symptoms [13,14]. While general dietary improvements are beneficial, understanding the specific impact of key nutrient-dense foods is vital for designing targeted and effective interventions [15]. Specifically, nuts may play a crucial role in healthy dietary patterns that have been associated with lower rates of depression [16,17,18] and improved mood in the general population. Nuts are characterized by their high nutrient density and are rich in bioactive compounds with anti-inflammatory, antioxidant, and neuroprotective potential [19,20]. They comprise a diverse range of varieties, including walnuts, almonds, hazelnuts, pistachios, and others. Nutritionally, they provide substantial amounts of monounsaturated fatty acids (MUFAs) and polyunsaturated fatty acids (PUFAs), including omega-9 oleic acid, the essential fatty acids omega-3 alpha-linolenic acid, and omega-6 linoleic acid, as well as high-quality plant protein, fiber, polyphenols, melatonin, vitamins, and minerals [19,21,22].

The proposed mechanisms indicate that nut compounds may alleviate depressive and anxiety symptoms through multiple pathways, including reducing systemic inflammation, attenuating oxidative stress, and modulating the gut-brain axis [23,24]. Moreover, the benefits of nut consumption may extend to other health-related aspects. Preliminary evidence suggests that nuts may increase sleep quality, which is likely attributable to their melatonin content [25], a neurohormone critical for regulating the sleep–wake cycle [26]. In terms of cognitive function, high levels of PUFAs and antioxidants in nuts may improve vascular elasticity and endothelial function in cerebral vessels and have immunomodulatory properties, which potentially promote neurogenesis and neuroplasticity [24,27]. Brain-derived neurotrophic factor (BDNF) has received increasing attention as the most abundant and widely expressed neurotrophin in the central nervous system and plays an important role in neural and cognitive function [28]. Peripheral BDNF levels have been associated with several mental health conditions, such as depressive disorders, anxiety, insomnia, eating disorders, and cognitive impairment [29,30,31,32]. BDNF levels are potentially modifiable through lifestyle [33] with some diet patterns, such as Mediterranean, showing increased circulating levels [34,35]. However, it has not yet been demonstrated whether the relationships between nut consumption and mental health or cognitive function are indeed mediated by biomarkers of inflammation, oxidative stress, BDNF [36], and other cardiometabolic risk factors, such as blood pressure and adiposity.

In this line, the current evidence base remains limited, methodologically heterogeneous, and insufficient for establishing robust dietary recommendations. It is still uncertain whether the observed benefits of nuts on mental health outcomes can be attributed to nut consumption per se or are instead confounded by cooccurring health-promoting behaviors, such as higher overall dietary quality, greater engagement in physical activity [37], better sleep patterns [38] and improved weight management [39], which are frequently reported among habitual nut consumers. Moreover, although a daily intake of 30 g is generally regarded as the minimum effective dose for cardiovascular protection [40], the potential existence of a dose–response relationship in relation to mental health outcomes has not been systematically investigated. This evidentiary gap highlights the need for rigorously designed randomized controlled trials (RCTs) that incorporate extended follow-up periods to generate robust empirical data capable of informing specific and evidence-based recommendations regarding the potential effects of nut consumption on mental health. In addition, the predominance of studies conducted in older adults, largely within the context of preventing cognitive decline [41], highlights a substantial gap in evidence concerning younger adult populations.

Early adulthood is characterized by substantial physical, psychological, and social transitions and frequently coincides with the onset of mental health problems [42,43]. This developmental stage merits particular attention, as early manifestations of mental health symptoms are closely associated with adverse physical and psychological outcomes later in life [44]. Furthermore, lifestyle behaviors established during this period exert a sustained influence on subsequent mental health trajectories [45,46]. Within this context, developing a more comprehensive understanding of the relationship between nut consumption and mental health symptoms in early adulthood is essential for informing evidence-based strategies aimed at promoting mental well-being across the lifespan.

The Nuts4Brain-RCT provides several distinctive contributions beyond existing trial designs. In contrast to previous studies, which have primarily focused on preventing cognitive decline and dementia in older adults [37,47] or have relied on observational evidence [17,18], this protocol targets young adults aged 18–24 years, a critical developmental period for mental health [48,49]. Regarding the three available RCTs on nut consumption and mental health associations in young populations, Pribis et al. [50] examined the effects of walnut consumption (1/2 cup or 60 g) on mood and cognitive performance among young adults. They found a significant medium effect size improvement in mood among males (Cohen’s d = 0.708, *p* = 0.043), but no significant changes were found for females or when both sexes were combined, as observed in another article with data from the same RCT [51]. Additionally, an increase in inferential verbal reasoning (d = 0.567; *p* = 0.009) was found, but no significant increases were detected in memory or non-verbal reasoning ability [50]. Herselman et al. (2022) [48] examined the effects of daily walnut consumption (56 g/day for 16 weeks) and academic stress on mental health in university students. A significant decrease in feelings associated with depression was found in women who consumed walnuts compared to controls; however, male data were not analyzed due to low participant numbers. In addition, Pinar-Martí et al. [49] studied the effect of walnut consumption (30 g/day for six months) on neuropsychological development in adolescents. Although no improvements in neuropsychological function were found when comparing the intervention and control groups, some benefits were observed in variables such as sustained attention and fluid intelligence among participants with better adherence to the intervention. The key methodological innovation is the dose–response design (30 g/day vs. 60 g/day), addressing the current lack of evidence on optimal nut intake for mental well-being. Moreover, whereas many prior trials have assessed isolated outcomes, this study adopts a comprehensive and integrative approach by combining psychometric assessments, objective cognitive testing, and biological markers related to underlying mechanisms. Finally, the inclusion of a 12-month follow-up (comprising a 6-month intervention and a 6-month post-intervention period) allows for the evaluation of the sustainability of effects, thereby distinguishing this protocol from shorter-term interventions.

Therefore, the Nuts4Brain-RCT study aims to evaluate the impact of a 6-month intervention involving nut consumption on depressive and anxiety symptoms, perceived stress, cognitive functioning, sleep quality, overall well-being, health-related quality of life, and biochemical mediators of brain function in young adults. The present manuscript constitutes a pre-results protocol publication documenting the study design, procedures, and analytical plan prior to participant recruitment and data collection.

## 2. Methods

This randomized controlled trial protocol is derived from the “Nuts4Brain project: The relationship between nut consumption and mental health outcomes during adulthood” (reference PI21/01898), co-funded by the European Union and the Carlos III Health Institute, Spain.

The study was designed in accordance with the Standard Protocol Items: Recommendations for Interventional Trials (SPIRIT) guidelines [52,53], which offer a rigorous framework for the development and transparent reporting of clinical trial protocols.

### 2.1. Ethical Aspects

The Nuts4Brain-RCT study protocol adhered to the principles of the Declaration of Helsinki [54] and the Singapore Statement on Research Integrity [55] and obtained approval from the Clinical Research Ethics Committee of the Virgen de la Luz Hospital (REG: 2025/E0125) and has been registered at ClinicalTrials.gov (NCT07292610). All interested participants will be required to sign an informed consent form prior to participation in the study.

### 2.2. Study Design

A 6-month, randomized, single-blinded, three-arm parallel-group clinical trial will be conducted in young adults (aged 18–24 years). The participants will be randomly assigned in a 1:1:1 ratio to one of three groups: (1) a control group maintaining their habitual diet while avoiding nut consumption; (2) a 30 g/day mixed-nut consumption group; or (3) a 60 g/day mixed-nut consumption group while avoiding nut consumption from other sources.

As illustrated in Figure 1, outcomes and other relevant variables will be assessed at baseline, 3 months after the beginning of the intervention, 6 months (i.e., at the end of the intervention), and 6 months after the end of the intervention, resulting in a total of data collection points over 12 months.

### 2.3. Eligibility Criteria

The inclusion criteria will be as follows: (1) being enrolled as a university student in any undergraduate academic program at the University of Castilla-La Mancha (UCLM), campus of Cuenca; (2) aged between 18 and 24 years; and (3) being willing and able to provide written informed consent to participate.

The exclusion criteria will include any known food allergies, particularly tree nuts or peanuts; chronic psychiatric or gastrointestinal medical conditions diagnosed and/or under pharmacological treatment; and the expected inability to attend follow-up visits because of planned internship abroad or study completion during the trial period. Those who are pregnant at the time of randomization or who plan to become pregnant during the follow-up period will be ineligible.

### 2.4. Sample Size Calculation

The sample size was calculated using the Grayling and Wason method for multi-arm trials [56], which is appropriate for a design with two experimental groups and one control group. A medium effect size (Cohen’s d = 0.5) and homogeneity of variance (σ = 1) were assumed across groups as recommended [57] when no clear estimate on this association is provided in the available studies with similar design [48,49]. With a two-sided α of 0.05 and 80% power (β = 0.20), the required sample size was obtained via the “des_ss_norm()” function in R statistical software, version 4.5.2 (R Core Team, 2024, Vienna, Austria). All three arms were allocated at a 1:1:1 ratio. To account for multiple comparisons, the Benjamini–Hochberg correction was applied to control the false discovery rate. The power calculation was based on a disjunctive criterion, which estimates the probability of detecting at least one significant difference between any intervention group and the control group. The initial calculation yielded a requirement of 42 participants per group. After accounting for an anticipated 20% dropout rate, the final sample size was adjusted to 53 participants per group. This resulted in a total target enrollment of 159 participants across all three study arms. The participants will initially be drawn from the 463 students enrolled in the Nuts4Brain-Z observational study (data collection September–December 2023) [58,59,60]. If necessary, recruitment will be extended to additional UCLM undergraduate students to reach the target sample size.

The sample size calculation was based exclusively on the primary outcome as we did not find previous studies examining the association between nut consumption and our secondary outcomes that would provide the necessary effect size estimates for power and sample size calculations. Consequently, the study should be considered exploratory with regard to these secondary outcomes, and any findings related to them should be interpreted with appropriate caution. While our sample size provides adequate power for detecting changes in the primary outcome, we acknowledge that it may be underpowered for detecting meaningful differences in secondary outcomes, particularly if the true effects are small to moderate in magnitude.

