Limitations include the inability to blind participants due to the whole-food nature of the intervention, which may introduce performance or expectation bias. To minimize these biases, a multi-layer strategy will be implemented. First, allocation will be strictly concealed using opaque, sealed envelopes until baseline assessments are completed. Following randomization, outcome assessors and data analysts will remain blinded to group allocation throughout the trial. During the intervention period, compliance will be monitored via blood vitamin E concentrations. At assessment points, self-reported mental health measures (BDI-II, GAD-7) will be complemented with objective cognitive assessments (NIH Toolbox) and biological markers (BDNF, inflammatory markers, cortisol). Together, these measures help mitigate expectancy effects and strengthen the trial’s internal validity. The recruitment of university students enhances sample homogeneity but may also restrict the generalizability of the findings to broader young adult populations. Finally, although the study is powered to detect medium effect sizes, mental health outcomes are multifactorial and may be influenced by unmeasured genetic or environmental factors.

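### The 42 per group matches a one-sided 0.05 test; with the stated two-sided 0.05 it gives about 70% power, not 80%

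*Protocol article*

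**What the plan says.** Section 2.4 of the protocol article gives a complete set of inputs and one result.

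- Design: "a design with two experimental groups and one control group", and "All three arms were allocated at a 1:1:1 ratio".
- Effect and variance: "A medium effect size (Cohen’s d = 0.5) and homogeneity of variance (σ = 1) were assumed across groups".
- Error rates: "With a two-sided α of 0.05 and 80% power (β = 0.20), the required sample size was obtained".
- Multiplicity: Benjamini–Hochberg correction.
- Power definition: "The power calculation was based on a disjunctive criterion, which estimates the probability of detecting at least one significant difference", between any intervention group and control.
- Result: "The initial calculation yielded a requirement of 42 participants per group". A 20% dropout allowance raises this to 53 per group, 159 in total.

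The same section then says that the sample has adequate power for the primary outcome. The Discussion (Section 3) repeats the claim: "although the study is powered to detect medium effect sizes".

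**The concern.** For one two-sided 0.05 comparison with d = 0.5, the usual normal-approximation formula already needs 63 per group for 80% power. Counting a win on either of two doses lowers that number, and a multiplicity correction raises it again. A result of 42 looked too small for a two-sided test, so the calculation was repeated from the stated inputs.

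If 42 is wrong for the stated test, the headline power is overstated. The dropout allowance no longer protects 80% power but is needed to reach it. A reader who takes 80% at face value would also put too much weight on a null result. This matters here because Section 2.11 plans a contrast of each nut group with control, and the Introduction presents the dose–response comparison as the key innovation.

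**Working it through.** **Inputs (all from Section 2.4):** n = 42 per group, 1:1:1, d = 0.5, σ = 1, α = 0.05, two contrasts against one control, Benjamini–Hochberg, power for at least one significant contrast. The section gives a single d. I apply it to both doses, which is an assumption, although the natural one.

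**Test statistics.** Each contrast has a z statistic with mean d / √(2/n) and variance 1. Sharing the control with equal group sizes makes the correlation between the two 0.5. At n = 42 the mean is 0.5 / √(2/42) = 2.291.

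**Rejection rule.** With two tests, Benjamini–Hochberg rejects at least one hypothesis if the smaller p ≤ 0.025 or the larger p ≤ 0.05. Hence

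power = P(at least one z ≥ c₁) + P(both z lie between c₂ and c₁),

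where c₁ is the critical value for p = 0.025 and c₂ that for p = 0.05. For the two-sided test the opposite tail is negligible when both doses have d = 0.5.

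**Reproducing the plan's figure (one-sided 0.05):** c₁ = 1.960, c₂ = 1.645.

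- n = 42: 0.787 + 0.015 = 80.2%
- n = 41: 0.778 + 0.016 = 79.4% (from unrounded terms)

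So 42 is the smallest n that reaches 80%, exactly as reported.

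**The test as stated (two-sided 0.05):** c₁ = 2.241, c₂ = 1.960.

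- n = 42: 0.686 + 0.014 = 70.0%
- n = 52: 79.2%
- n = 53: 79.95%, that is, on the boundary
- n = 54: 80.7%

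Simulation agrees with the bivariate normal calculation. Pooled-variance t tests lower the two-sided figures slightly: about 69% at 42, 79% at 53 and 80% at 54.

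**Could another choice explain 42?** Two-sided, d = 0.5 in both doses:

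| Correction | Power at 42 | n for 80% |
|---|---|---|
| None | 78.7% | 44 |
| Benjamini–Hochberg (stated) | 70.0% | 53–54 |
| Dunnett | 69.8% | 54 |
| Bonferroni or Holm | 68.7% | 55 |

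No two-sided option in this table gives 42. One-sided Dunnett also gives 42 (80.1%), but it is again one-sided and is not the stated correction.

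**Dropout.** 42 / 0.8 = 52.5, rounded up to 53, and 3 × 53 = 159, so this step is correct. The 53 enrolled is, however, also roughly what the two-sided test needs as completers. Keeping 54 completers after 20% loss would take 54 / 0.8 = 67.5, that is 68 per group or 204 in total.

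**Other readings of power at 42 completers (two-sided, Benjamini–Hochberg, d = 0.5 in both doses):** a given dose significant, 59%; both doses significant, 47%.

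**The case against.** **The planned analysis may be more precise than the calculation.** Section 2.11 plans a repeated-measures mixed model. If it uses the baseline value, residual variance falls by a factor of about 1 − r², where r is the correlation between baseline and outcome. The protocol gives no r. Taking it as an assumption, two-sided power at 42 per group would be 74% at r = 0.3, 78% at 0.4, 80% at 0.46, 82% at 0.5 and 88% at 0.6. Intention-to-treat analysis with incomplete observations also keeps some information from people who leave after month 3. This stands as a limit on the conclusion: the power of the final analysis is unknown and could reach 80%. It does not rescue Section 2.4, which takes no credit for such a gain and reports 42 as the result of its own inputs.

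**The effect in each dose is not spelled out.** This is fair, and power is sensitive to it. If only one dose has d = 0.5, two-sided power at 42 falls to about 53%. If the 60 g group had 0.6, in line with the modest extra benefit that the Discussion expects, power would be 79%. An effect of 0.5 in both doses is the natural reading and a favourable one, and it is also the reading under which 42 reproduces with a one-sided test.

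**The disjunctive definition is disclosed.** This is correct. The lower power for a given dose is not an error in the text, and the finding does not depend on it. It is useful added information.

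**The cause is inferred.** The function call is not shown, so a one-sided setting is the likely explanation, not an established one. The mismatch between inputs and result holds whatever the cause.

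**Conclusion.** The point holds. With the inputs that Section 2.4 states, 42 per group gives about 70% power (69% with t tests) against a claimed 80%, and 80% needs 53 to 54 completers per group (54 to 55 with t tests). The shortfall is about 10 percentage points of power, or 11 to 12 completers per group. Under the stated correction, 42 is reproduced only with a one-sided 0.05 level.

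This rests on d = 0.5 in both doses, SD 1, and one unadjusted comparison at a single time point, which is what the section describes. It shows that the reported calculation is wrong as written. It does not show what power the mixed model will have. The claims of adequate power and of being powered for medium effects are not supported by the calculation offered for them.

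**What to change.** Rerun the sample size function with the sidedness made explicit, then correct Section 2.4 in one of two ways:

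1. Keep two-sided 0.05 and state that 42 completers per group, with Benjamini–Hochberg and d = 0.5 in both doses, give about 70% power for at least one dose and about 59% for a given dose.
2. State that the calculation used one-sided 0.05, and make the significance level in Section 2.11 consistent with it.

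In either case, say that d = 0.5 is assumed for both doses, and bring the power claims in Section 2.4 and the Discussion into line. If the authors want to rely on a gain from baseline adjustment or repeated measures, they should state the assumed correlation and show the resulting power.

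The cost is one function call and a few sentences, and under the first option a less favourable stated power. No change in enrolment is required. The article describes itself as written before recruitment, so the correction can be made before any data are collected.

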The results will be considered statistically significant at the α = 0.05 level. In the presence of statistically significant effects, post hoc analyses will be conducted using a pairwise comparison test to delineate specific contrasts between each intervention group and the control arm. Furthermore, statistical and clinical significance will be distinguished in our discussion, considering both the magnitude of effects and their potential implications for guidelines recommending nut consumption as a strategy to prevent or improve mental health outcomes. Therefore, when the estimators of associations do not reach statistical significance due to the small difference between the intervention and control groups, the results will be presented for their descriptive value and to inform future RCTs exploring the relationship between nuts and mental health. Although *p*-values are relevant, changes that are not statistically significant can still be clinically meaningful [104].

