Specifically, daily consumption of 30 g of mixed nuts for six months is expected to result in a decrease in the frequency, severity, and number of depressive symptoms and a reduction in anxiety and stress levels, alongside improvements in mental well-being, cognitive function, and sleep quality. The participants who will consume 60 g/day are anticipated to demonstrate a modest increase in these benefits, reflecting a potential dose–response effect. This hypothesis is based on biological plausibility, suggesting that a higher intake of certain compounds (e.g., polyphenols and omega-3 fatty acids) may exert stronger anti-inflammatory, antioxidant and neuroprotective effects required to modulate brain function [19,23]. Additionally, the intervention is expected to improve overall diet quality, maintain body weight (with possible minor reductions in body fat percentage and waist circumference), and enhance metabolic health, including improved lipid profiles, lower blood glucose levels, and reduced inflammatory markers, compared with those of the control group.

This protocol presents several key strengths. First, its randomized controlled design with a dose–response approach addresses a critical evidence gap regarding the “optimal dose” of nut consumption for enhancing mental well-being. Second, the study adopts a multidisciplinary assessment strategy that integrates validated psychometric scales (BDI-II, GAD-7), comprehensive neuropsychological evaluations, and biochemical validation (BDNF). Third, the intervention extends over a six-month period, providing a sufficiently long timeframe to observe meaningful effects. In addition, a fourth visit will be carried out six months after the end of the intervention to evaluate whether nut consumption and its potential effects persist over time. Fourth, adherence will be rigorously monitored through the provision of prepacked nut portions and objective verification via plasma vitamin E levels, thereby increasing compliance in a manner that overcomes challenges typically associated with dietary interventions. Finally, relevant variables (habitual dietary intake, physical activity, fitness, etc.) will be examined for moderating, mediating, or confounding effects.

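### The 80% in section 2.4 is the chance that at least one dose beats control, but sections 2.4 and 3 claim power for medium effects without that limit; power for a named dose is about 10 to 11 points lower on the same test

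*Protocol article*

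**What the plan says.** Section 2.4 sets the inputs: "A medium effect size (Cohen’s d = 0.5) and homogeneity of variance (σ = 1) were assumed across groups", and "With a two-sided α of 0.05 and 80% power (β = 0.20"), with 1:1:1 allocation and a Benjamini–Hochberg correction. The criterion is disclosed: "The power calculation was based on a disjunctive criterion, which estimates the probability of detecting at least one significant difference between any intervention group and" control. The result is 42 per group, raised to 53 for 20% dropout, 159 in all.

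Two later sentences drop the limit. Section 2.4 itself goes on: "While our sample size provides adequate power for detecting changes in the primary outcome". The limitations paragraph of the Discussion (section 3) says "although the study is powered to detect medium effect sizes".

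The inferential aim is dose-specific. Section 2.11 plans pairwise tests, after a significant effect, to "delineate specific contrasts between each intervention group and the control arm". The Discussion expects benefit at 30 g/day and adds: "The participants who will consume 60 g/day are anticipated to demonstrate a modest increase in these benefits".

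**The concern.** Disjunctive power answers one question: will at least one of two comparisons succeed? With two chances, it is always at least as high as the power for either comparison alone. The article computes the first quantity and then words its power claims as though it had the second.

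The 30 g against 60 g comparison is presented as the trial's main methodological novelty, so readers will want a conclusion about each dose. Someone who sees a non-significant 30 g contrast next to a statement that the trial was powered for medium effects may take it as evidence, at about 80% power, against a medium effect at 30 g. The calculation in section 2.4 does not give that assurance for either dose. Section 2.11 links the results to guideline implications, so the distinction has practical weight.

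**Working it through.** **Inputs.** All from section 2.4: n = 42 evaluable per arm, d = 0.5 at both doses, SD 1, 1:1:1 allocation, alpha 0.05, Benjamini–Hochberg. My assumptions: a single-endpoint z-comparison, the correction applied over the two dose–control contrasts, and no gain from baseline or earlier visits.

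**Model.** Each dose–control statistic Z has mean d × √(n/2) and variance 1. The shared control arm with equal allocation gives correlation 0.5. At n = 42 and d = 0.5 the mean is 0.5 × √21 = 2.291.

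**Rejection rule.** Both contrasts are significant if the larger p-value is at most 0.05. Otherwise the smaller one is significant if it is at most 0.025. The critical values are 1.645 and 1.960 one-sided, or 1.960 and 2.241 two-sided.

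**The plan's own figure.** By numerical integration, one-sided disjunctive power is 79.35% at n = 41 and 80.21% at n = 42, so 42 is exactly the minimum. Two-sided, as the text states, it is 70.04% at n = 42, and the minimum is 54. (Two-sided with no correction gives 78.7% at 42 and a minimum of 44, but the text says a correction was applied.) Dropout: 42/0.8 = 52.5, so 53; 3 × 53 = 159. Both agree with the article.

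**Power for a named dose, both doses at 0.5, n = 42:**

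| Test | At least one dose | A named dose | Both doses | Gap, first minus second |
|---|---|---|---|---|
| One-sided 0.05 | 80.21% | 70.53% | 60.86% | 9.68 |
| Two-sided 0.05 | 70.04% | 58.67% | 47.29% | 11.37 |

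Independent simulations agree to within about 0.1 point.

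**Hand checks.**
- With equal effects, named-dose power is the mean of the other two: (80.21 + 60.86)/2 = 70.53 (rounding down from 70.535) and (70.04 + 47.29)/2 = 58.67 (from 58.665).
- Named-dose power must lie between a Bonferroni test and an uncorrected one. One-sided: Φ(2.291 − 1.960) = 63.0% and Φ(2.291 − 1.645) = 74.1%. Two-sided: Φ(2.291 − 2.241) = 52.0% and Φ(2.291 − 1.960) = 63.0%. So even with no correction, a single contrast at d = 0.5 does not reach 80% with 42 per arm.

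**Unequal effects.** The article gives no sizes for its expected ordering, so these are illustrations (two-sided, n = 42):

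| 30 g, 60 g (assumed) | At least one | 30 g | 60 g |
|---|---|---|---|
| 0.4, 0.5 | 62.1% | 41.7% | 56.4% |
| 0.5, 0.5 | 70.0% | 58.7% | 58.7% |
| 0.5, 0.6 | 79.2% | 60.7% | 74.0% |

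**Baseline adjustment.** With an assumed correlation ρ between baseline and endpoint, the effective n is 42/(1 − ρ²): 56 at 0.5, 65.6 at 0.6 and 82.4 at 0.7. Two-sided named-dose power (both doses at 0.5) is then about 72%, 79% and 88%. Reaching 80% takes 67 per arm unadjusted, so 1 − ρ² = 42/67 = 0.627 and ρ is about 0.61.

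**The gate.** Section 2.11 makes the dose contrasts only after a significant effect. Requiring an extra significant result cannot raise named-dose power, so the figures above are not lowered by leaving it out.

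**The case against.** The strongest reply is that nothing is hidden. Disjunctive power is a recognised criterion for multi-arm trials, section 2.4 defines it, and the common d = 0.5 is stated. The dose contrasts come after a significant effect, and an at-least-one criterion is reasonably close to such a gate. Section 2.11 also says non-significant results will be shown for descriptive value and may still be clinically meaningful. The limitations section admits low power for small effects. Finally, the planned mixed model may use baseline and earlier visits, so an endpoint-only figure may be pessimistic.

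Most of this stands. The choice of criterion is legitimate and is not an arithmetic error. The promised reading of null results reduces the harm, though it does not tell the reader that the power claim excludes single-dose conclusions. The adjustment argument is sound in principle, but the article states no correlation and claims no gain from it. None of it supports the two unqualified sentences.

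Two stronger readings are tempting and should be resisted.
- A reader might set the article's 80% beside 58.7% and attribute the whole 21 points to the disjunctive criterion. About 10 of those points (80.2 to 70.0) arise because 42 is a one-sided result labelled two-sided. That is a separate defect, and adding it here would count it twice.
- A reader might infer that the expected ordering of doses necessarily lowers power. The article gives no effect sizes, and the ordering is as compatible with 0.5 and 0.6, where disjunctive power rises, as with 0.4 and 0.5, where it falls.

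**Conclusion.** The point holds in limited form. The calculation supports a claim about at least one dose when both have d = 0.5. The general statements in section 2.4 and the Discussion go further. On a like-for-like test, power for a named dose is 9.7 points (one-sided) or 11.4 points (two-sided) below the disjunctive figure. Under the two-sided test the article states, this means about 59% against about 70%.

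These sizes rest on 42 evaluable per arm, d = 0.5 at both doses, SD 1, Benjamini–Hochberg over two contrasts, and a simple endpoint comparison. With no dropout (53 per arm), two-sided named-dose power would be 69.7%. A baseline correlation above about 0.6 could bring it near 80% at 42 per arm, but the documents do not allow that to be assumed. The matter is one of accurate reporting and later interpretation; it does not show that the design is invalid.

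**What to change.** Keep enrolment as planned and change the text:

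1. In section 2.4, report disjunctive and named-dose power side by side on one stated sidedness. Two-sided at 42 per arm these are about 70% and 59%, before any gain from baseline or repeated measures. If such a gain is claimed, state the assumed correlation. Do not print 80% (a one-sided figure) beside 59% (a two-sided one).
2. Limit the adequate-power sentence in section 2.4 and the medium-effect sentence in the Discussion to detecting at least one dose if both have d = 0.5.
3. In section 2.11, state that a non-significant result for a single dose will be read from its confidence interval and not taken as evidence against a medium effect at that dose.

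The cost is a few sentences. Recruitment, conduct and the analysis model do not change, and the article describes itself as written before recruitment. The downside is that the stated power becomes less favourable.
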